**Methods:**

The Internet-Based Lifestyle Intervention to Eradicate Obese Frailty in Prostate Cancer Survivors (iLIVE) Randomized Controlled Trial (RCT) aims to mitigate obese frailty among men with prostate cancer treated with ADT. Participants (N=250) are being recruited across North America to participate in this RCT that is implemented entirely over the internet. Eligibility criteria include body mass index >25 kg/m2 and > 2 frailty symptoms [illness, fatigue, inactivity, weakness, slowness]). Consented participants undergo assessments that include: online surveys (medical status, falls, physical activity, quality-of-life, healthcare utilization); dietary recalls (kilocalories, diet quality); body weight (Aria® scales); physical activity (Fitbits®); 4) internet-based physical performance (chair stand, timed up-and-go, gait speed tests); and 5) muscle mass (D3 creatine dilution). Participants are then randomized to one of two 6-month interventions: 1) Enhanced Usual Care (EUC): Encouraged to continue Aria® scale and Fitbit® use with monthly emails of publicly available diet- and exercise-related information; or 2) iLIVE: Same as EUC, plus website access to weekly serialized sessions on weight loss and diet quality and thrice-weekly live remote supervised group resistance training sessions. Assessments are repeated at 6-months; at 12-months, questionnaires are repeated and data from digital devices are captured. Intent-to-treat analysis will compare EUC vs. iLIVE (baseline-to-6-months) using a composite measure of obese frailty as the primary outcome. Designed as a type I hybrid-effectiveness implementation trial, data on intervention feasibility (including safety), acceptability, adoption, appropriateness, fidelity, sustainability, and cost are assessed, tracked, and analyzed.

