**Fig. 1 Fig1:**
[figure not shown]
iLIVE study design and flow diagram Legend: The intention-to-treat analysis will use all data from randomized participants who are not excluded due to death or the development of other serious subsequent conditions that affect body weight and function

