### Primary outcome

A reduction in the Obese Frailty Phenotype (OFP) score serves as the primary outcome and it is defined as clinically significant weight loss of 5% AND clinically meaningful change in 2 or more frailty components, i.e., weakness, slowness, fatigue, inactivity, and/or illness (see below). The OFP is a dichotomous binary score that indicates improvement when both elements are met (yes) or not (no).

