#### Safety

Participants are encouraged to report adverse events as they occur but are also queried monthly throughout the 12-month study period. The description of the event is collected, along with details on the medical care received, and whether the participant attributed it to exercise associated with either study intervention or whether they attributed it to dietary changes they were undertaking to reduce their caloric consumption, e.g., indigestion due to higher intakes of plant-based foods. These events are reviewed quarterly by the study team who are blinded to arm assignment and who classify events as serious (i.e., life threatening, permanently disabling, and/or resulting in overnight hospitalization) or non-serious, and attributable, possibly attributable, or non-attributable to the intervention. Obvious serious events are evaluated within 72-hours by the trial MPI’s with assistance from co-investigators with certified medical training and reported to the OHSU Institutional Review Board (IRB). All events are reviewed annually by the OHSU IRB, as well as an independent Data Safety and Monitoring Board (comprised of a biostatistician, clinician-scientist, and a patient advocate) to confirm adherence to safety standards and assess any imbalances between study arms. No interim analyses are planned.

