#### Planned data analysis

##### Quantitative data analysis

Once data collection is complete, study retention will be examined to determine between-arm differences and explore potential differences between drop-outs and study completers. Study data will be examined using standard descriptive statistics and graphics to check for distributional assumptions, the presence of outliers, and patterns of missingness to inform final modeling strategies (e.g., the use of model-based maximum likelihood estimation) [57]. All analyses will be conducted using an intention-to-treat approach (using all data from randomized participants who are not excluded due to death or the development of other serious subsequent conditions that affect body weight and function) using R v3.3.2171 9 (R foundation, Vienna, Austria) and Mplus v7.31172 (Los Angeles, CA) software. In addition to traditional significance testing, Cohen’s d or odds ratio effect sizes (with 95% confidence intervals), as appropriate, will be estimated for change in primary and secondary endpoints across time. Model diagnostics (e.g., examining residual/predicted value plots) will be used to confirm statistical assumptions have been met. In the case of violations, more robust estimation procedures, such as nonparametric bootstrapping, will be employed as appropriate.

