Standard logistic regression models will be used to test between-arm differences for both the primary and secondary binary outcomes. Complementary analyses will be conducted on each continuous frailty component separately using a linear mixed effects modeling approach implemented in the R lme4 package. Contemporary methods will be used to control for false discovery rates when testing secondary outcomes [58]. Durability of the effect of iLIVE vs. the EUC intervention after the structured program stops (i.e., at 6 months), will be explored in a limited number of outcomes (e.g., body weight, physical activity and self-reported measures of fatigue and quality of life using baseline to 12-month data). Time will be modeled either as a fixed effect with two contrasts comparing baseline to 6-month, and baseline to 12 month follow up or as a piecewise model with separate estimates of change between baseline and 6 months and 6 months and 12 months. The primary effects of interest will be the cross-level interactions between intervention group (fixed binary predictor) and the time contrasts. Significant interactions will indicate that outcome change across time differs between the intervention groups. Potential moderators (e.g., age, BMI, time from diagnosis) will be explored by adding these terms to the models and testing for interaction. These analyses will allow us to determine the characteristics of patients who have the highest likelihood of change. We also have experience using Latent Class Analysis on longitudinal change estimates to discover clusters of intervention responders [59].

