##### Cost analysis

In addition to the descriptive calculation of costs, a within trial cost-effectiveness analysis will compare the implementation costs net of health care cost savings (if any) to the effectiveness of iLIVE vs. EUC on the gain in QALYs calculated using utility weights derived from the EQ-5D [34, 60]. Health care savings will be determined by comparing health care costs derived from self-reported health care utilization data between the two study arms [35]. Regression analysis, or non-parametric bootstrap techniques if data are skewed, will estimate differences in QALYs and health care costs between iLIVE and EUC [61, 62]. An incremental cost effectiveness ratio will be calculated and compared to common thresholds to determine if iLIVE is cost-effective compared to EUC [63, 64].

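### The analysis labelled intention-to-treat excludes randomised men who die or become seriously ill after randomisation, so the primary comparison is mislabelled and can be biased in either direction

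*Protocol article*

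**What the plan says.** Under Quantitative data analysis, the protocol article states that "All analyses will be conducted using an intention-to-treat approach". The same sentence then restricts the data to "randomized participants who are not excluded due to death or the development of other serious subsequent conditions that affect body weight and function". The Fig. 1 legend gives the same rule: "The intention-to-treat analysis will use all data from randomized participants who are not excluded due to death", followed by the same second ground. The abstract describes the primary analysis without any exclusion: "Intent-to-treat analysis will compare EUC vs. iLIVE (baseline-to-6-months) using a composite measure of obese frailty as the primary outcome".

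The OFP is binary. Under Primary outcome, success needs 5% weight loss together with meaningful change in at least two of five frailty components, one of which is illness. On the test, the plan says: "Standard logistic regression models will be used to test between-arm differences for both the primary and secondary binary outcomes".

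Two neighbouring sections bear on how far the rule reaches. Safety defines serious events as "life threatening, permanently disabling, and/or resulting in overnight hospitalization" and has all events reviewed by the IRB and an independent monitoring board, including for imbalance between arms. Cost analysis has its own heading and names no analysis set: "Health care savings will be determined by comparing health care costs derived from self-reported health care utilization data between the two study arms".

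**The concern.** Intention-to-treat keeps every randomised man in the arm he was assigned to. Both grounds for exclusion here arise after randomisation, and three features make that matter.

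- **Exclusion can depend on the arm.** iLIVE adds weight loss and thrice-weekly resistance training with weighted vests up to 15% of body weight. The consent form details the risks of diet change and activity, and adverse events are queried for attribution to either. The programme might cause some excluding events. It might also prevent some, since falls and related injuries are an outcome.
- **The criterion overlaps the endpoint.** Removing men for illness that affects weight and function selects on the same domains that the OFP measures.
- **The label hides it.** A reader of the abstract would expect all randomised men in the denominator.

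At stake is whether the headline result compares the groups as randomised. Men removed this way would mostly be treatment failures, and they would leave the denominator instead of counting against their arm.

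**Working it through.** **Inputs from the article** (Power and sample size calculation): 125 randomised per arm; 100 complete cases per arm; expected response 40% vs 10%; detectable difference 18–20 points; two-sided alpha 0.05; power 0.80; attrition about 20%.

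**Assumed inputs:** the numbers excluded, since the article gives none; that excluded men are non-responders; and, in step 2, a response of 28% vs 10% (the stated 10% control rate plus the lower end of the detectable range).

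**1. The plan's own figures.** Required n per arm = [1.96·√(2p̄(1−p̄)) + 0.8416·√(p₁(1−p₁) + p₀(1−p₀))]² / (p₁−p₀)².
- 38% vs 20%: (1.258 + 0.529)² / 0.0324 = 98.6, so 99 per arm.
- 60% vs 40%: (1.386 + 0.583)² / 0.04 = 96.9, so 97 per arm.
- Total: 200 / (1 − 0.20) = 250.

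The 18–20 point range and N = 250 both reproduce. From a 10% control rate, 100 per arm detects 15.0 points, so the stated range is conservative there.

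**2. Effect of the exclusion on the estimate.** The rate among retained men is x / (125 − e), where x is the expected number of responders (35 and 12.5) and e the number excluded.

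| Excluded, iLIVE / control | iLIVE | Control | Difference |
|---|---|---|---|
| 0 / 0 | 35/125 = 28.0% | 12.5/125 = 10.0% | 18.0 points |
| 8 / 3 | 35/117 = 29.9% | 12.5/122 = 10.2% | 19.7 points |
| 5 / 5 | 35/120 = 29.2% | 12.5/120 = 10.4% | 18.8 points |
| 0 / 8 | 35/125 = 28.0% | 12.5/117 = 10.7% | 17.3 points |

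Equal exclusion still inflates a true difference, by the factor 125/120. Exclusion confined to the control arm shrinks it.

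**3. Effect on the test when there is no true difference.** Let r be the common response among all randomised men. Retained rates are r/(1−e₁) and r/(1−e₀), where e is now the fraction excluded, on 125(1−e₁) and 125(1−e₀) men. Rejection rates use the normal approximation to the pooled two-proportion test, as a stand-in for the logistic model.

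| r | Excluded, iLIVE / control | Spurious difference | Actual alpha |
|---|---|---|---|
| 25% | 5% / 5% | 0 | 0.050 |
| 25% | 10% / 5% | +1.5 points | 0.057 |
| 25% | 5% / 10% | −1.5 points | 0.057 |
| 25% | 10% / 0% | +2.8 points | 0.078 |
| 40% | 10% / 0% | +4.4 points | 0.107 |
| 10% | 10% / 0% | +1.1 points | 0.060 |

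**4. The planned effect with all men kept.** If 40% vs 10% holds among retained men and excluded men count as non-responders, the difference over all randomised men is 0.40(1−e₁) − 0.10(1−e₀):
- 5% / 5% excluded: 38.0 − 9.5 = 28.5 points.
- 10% / 10%: 36.0 − 9.0 = 27.0 points.
- 10% / 5%: 36.0 − 9.5 = 26.5 points.
- 5% / 10%: 38.0 − 9.0 = 29.0 points.

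**The case against.** The strongest defence is that the exclusion has a sensible aim. A man who has died has no 6-month OFP, and weight lost through advancing disease should not count as success. Exclusions may be few and balanced, in which case alpha stays at 0.05, and at the expected 40% vs 10% modest exclusions would not overturn the result. A list of conditions and an adjudication procedure may also sit in the full protocol or analysis plan.

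Much of this stands as a limit on size. It does not rescue the label or the set. The aim can be met without dropping anyone, and the OFP already guards against the main worry, because weight loss alone is not success without change in at least two frailty components. How conditions are adjudicated is no part of this point: a well-adjudicated exclusion after randomisation is still one. Counting these events as non-response is one of several defensible strategies, but it is explicit and keeps the randomised denominator.

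Three stronger readings are tempting, and the article does not support them.

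- **That safety is assessed on a selected set.** IRB and monitoring-board review covers all events and arm imbalances without exclusion. Only the final safety summaries could be touched, through the unqualified scope of the sentence.
- **That the costliest men are removed from the cost-effectiveness analysis.** Cost analysis is a separate heading and states no exclusion. It is covered only if the sentence is read literally across headings, and that sentence also prescribes software which the qualitative analysis plainly does not use. The scope is unclear, not established.
- **That the sample size leaves no room for these exclusions.** The trial is sized for 200 complete cases, and the roughly 20% attrition may already include men who die or fall ill.

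**Conclusion.** The point holds for the primary OFP comparison and the other analyses described under Quantitative data analysis. As written, the plan applies an intention-to-treat label to a set selected after randomisation, in two places, and the abstract does not disclose it.

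The size cannot be determined from the article. Under the assumed exclusions the estimate moves by about 1 to 2 points (18.0 to 18.8 or 19.7, or down to 17.3). Under no true difference, alpha ranges from 0.05 with equal exclusion to 0.107 in the most lopsided case tried. These figures assume that every excluded man is a non-responder. It should not be inferred that the rule favours iLIVE: the sign depends on which arm loses more men. The effect is modest unless exclusions differ clearly between arms, and it matters more near the 18–20 point differences the trial is powered for than at the expected 30 points. The sample-size arithmetic is sound. For safety and cost, the article needs only a clarification of scope.

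**What to change.** - Delete the exclusion clause under Quantitative data analysis and in the Fig. 1 legend. State that every randomised man is analysed in his assigned arm.
- For the OFP, count death or a serious new condition affecting weight and function before 6 months as non-response.
- Keep the present rule only as a sensitivity analysis, labelled as excluding men on events after randomisation.
- State that the exclusion does not apply to the final safety summaries or to the cost and QALY analysis. Use whatever data are available for these men, with utility 0 from death.

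For the primary analysis this costs wording only. The sample size does not change, and adverse events are already queried monthly. Observed response rates may be slightly lower, as step 4 of the working shows. For cost and QALYs, utilisation and EQ-5D are self-reported and the article does not say whether follow-up continues after exclusion, so some of these men's data may be incomplete.

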#### iLIVE intervention

The iLIVE intervention is an amalgam of previous interventions that have shown efficacy in improving diet quality and promoting weight loss, as well as increasing physical activity, especially aimed at improving strength and physical function, i.e., resistance training, among cancer survivors. The message library developed for the efficacy-proven Reach-out to Enhance Wellness (RENEW) intervention which was originally delivered via tailored print materials and telephone counseling to 641 breast, prostate and colorectal cancer survivors [41–43], was first adapted for web-use in the Daughters, dUdes, mothers and othErs Together (DUET) trial among 112 cancer survivors and chosen partners [44, 45], as well as the AiM, Plan and act on LIFestYles (AMPLIFY) trial (*n* = 351) [15, 46, 47], both of which confirmed efficacy. The web-based interventions which provide content that is refreshed routinely via tips of the day, weekly interactive sessions (tutorials), features to track dietary behaviors and body weight, and over 100 tools (e.g., meal plans, grocery lists, cooking videos) were adapted exclusively to meet the needs of prostate cancer survivors on ADT. Likewise, previous functional resistance training programs found effective in improving strength and reducing falls in supervised, facility-based group classes [48–50], were adapted to live remote instruction using standard videoconferencing software (e.g., Zoom), and led by a trained instructor who leads the exercises, modifies exercises for safety and tolerance, provides feedback on proper form, and offers encouragement. A second staff member is either online or on call during exercise sessions to assist with videoconferencing issues and/or safety monitoring. The resistance training program starts with several weeks of mobility and stability exercises designed to improve efficiency and safety of functional exercises that are the core of the functional strength training program. These mobility exercises are then integrated into the warm-up moving forward. The functional strength training program consists of a 60-minute session with a 5–10-minute warm-up, 45 min of functional resistance training, followed by a 5–10-minute cool down. The routine set of functional exercises consists of wall-sits, chair stands, step-ups, push-ups, rows, and core (e.g., plank, bird dog, bridge, dead bug) that are done during each session. As with prior facility-based programs, weighted vests are used to provide overload - an innovative method to progressively increase resistance in the lower body to improve musculoskeletal function without safety risks related to balance disruption that can occur with handheld weights. Given that the vest has multiple pockets distributed evenly around the torso with each holding a ½-lb weight, exercise intensity can be adjusted slowly and in an ergonomically efficient and safe way. The volume of resistance training progresses from the low-to-high moderate intensity range over the 24-week intervention using progression outlines in which vest weight (intensity) is gradually increased from 4% to 15% of body weight, while sets increase from 1 to 3 sets of 10–15 reps (as weight increases the rep range will decrease) [36, 48, 51]. Participants login thrice weekly, for 75-minute sessions that open 15 min prior to and after the exercise session to provide men with time and opportunity for personal interactions - a key element that provides valued peer support that can optimize adherence and retention. Social support, along with self-efficacy and reducing barriers to behavior change are key constructs of Social Cognitive Theory [39, 40], which serves as a unifying behavioral framework for both the physical activity and diet-related components of the iLIVE intervention.

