### Statistical analysis

#### Power and sample size calculation

The sample size requirements for this RCT were based on estimates obtained from an ongoing trial [36]. We estimated that 40% of men assigned to the iLIVE intervention vs. 10% of those assigned to usual care will demonstrate clinically significant improvements from baseline to 6-month follow-up in the obese frailty phenotype (defined as clinically significant weight loss of 5% and clinically meaningful change in 2 or more frailty components, i.e., weakness, slowness, fatigue, inactivity, and/or illness). However, we powered this trial to detect smaller effects that are likely still clinically meaningful. Assuming alpha=0.05 (two-tailed) and power=0.80, a sample size of 200 complete cases (100 in each group) would be required to detect proportional differences in the 18–20% range. Assuming an attrition rate of ~ 20%, the total sample size required is *N* = 250 (*n* = 125 in each group). If attrition is lower than expected, we will need to randomize fewer participants to achieve the desired sample size. Additionally, this sample size results in even more statistical precision when examining secondary outcomes that yield continuous data.

Sample sizes for the implementation analysis are based on estimates of achieving thematic saturation [55, 56]. Here, we anticipate interviewing 30 prostate cancer survivors (6 who refuse trial participation, 12 who enroll but drop out before the end of 6 months, and 12 who complete their 6-month assessment). Maximum variation sampling will be done based on study group allocation (enrollees only), age (< 75 vs. 75+) and region of the country (west vs. east). Plans also include interviewing eight oncology clinical care team members (different types of oncology providers and nurses) and eight health system administrators (Chief Executive Officers, etc.).

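### Only the iLIVE arm is delivered in live groups, so if outcomes correlate within classes the planned independent-men logistic model will understate the standard error of the arm effect

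*Protocol article*

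**What the plan says.** Randomization is of individual men, in blocks of six by current or past ADT (Protocol article, Randomization and interventions). The abstract describes the active arm as including "thrice-weekly live remote supervised group resistance training sessions". The iLIVE intervention section adds that a trained instructor leads the exercises, that a second staff member is online or on call, and that the session stays open before and after the exercise for "personal interactions - a key element that provides valued peer support that can optimize adherence and retention". The EUC arm gets devices, links and monthly newsletters, with no classes.

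For the primary and secondary binary outcomes, the Quantitative data analysis section states: "Standard logistic regression models will be used to test between-arm differences". Continuous frailty components get linear mixed models. No class or instructor term is mentioned for either.

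The Power and sample size calculation section sets a two-sided alpha of 0.05 and 80% power, and concludes that "a sample size of 200 complete cases (100 in each group) would be required". The targeted difference is 18 to 20 percentage points. It expects more than that: "We estimated that 40% of men assigned to the iLIVE intervention vs. 10% of those assigned to usual care" to improve. No ICC or design effect appears.

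**The concern.** This is a partially nested design: individual randomization, with grouping in one arm only. Men who share a class share its teaching, progression and company for 24 weeks, and the article itself names peer support as a working element. A good or poor class can therefore move several men's outcomes together. An ordinary logistic model counts each of those men as a separate piece of information. With a positive within-class correlation the iLIVE arm carries less information than the model assumes, so the standard error of the arm effect is too small. At stake are the coverage of the 95% intervals promised for the odds ratios, the 5% error rate, and some of the stated power.

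**Working it through.** **Inputs from the article.** Two-sided alpha 0.05; 100 complete cases per arm; attrition about 20%; expected response 40% versus 10%; detectable difference 18 to 20 points, with no control rate given for that range.

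**Inputs that are assumptions.** Class size m = 12, and ICC 0.02 to 0.05. The article gives neither, nor the number of classes or instructors, nor whether membership is fixed. Wider ranges are shown below.

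**1. The plan's own figure.** With independent men and 100 per arm, 80% power is reached at 17.9 points for a 20% control rate, 19.3 for 30% and 19.7 for 40%. 200 / (1 − 0.20) = 250. The stated figures reproduce, for independent men. At a 10% control rate the detectable difference is 15.0 points, so 18 to 20 is conservative there.

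**2. Standard error near the null.** The design effect in the iLIVE arm is DE = 1 + (m − 1) × ICC. The variance of the difference grows by (1 + DE)/2, since EUC is not grouped. The true error of the unadjusted test is 2 × [1 − Φ(1.96 / √((1 + DE)/2))].

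| m = 12 | DE | Variance ratio | SE ratio | True error |
|---|---|---|---|---|
| ICC 0.02 | 1.22 | 1.11 | 1.05 | 6.3% |
| ICC 0.05 | 1.55 | 1.275 | 1.13 | 8.3% |

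For other assumptions the formula gives 5.4% (m = 8, ICC 0.01), 7.7% (m = 10, ICC 0.05), 10.7% (m = 20, ICC 0.05) and 16.1% (m = 20, ICC 0.10).

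**3. The planned model at the article's control rate.** The formula is a large-sample approximation. Beta-binomial simulation (200,000 runs, 100 per arm, 12 per class, 10% rate in both arms) gives for the logistic Wald test about 4.2% with no clustering, 5.2% to 5.3% at ICC 0.02 and 6.9% to 7.0% at ICC 0.05. The score test, and the Wald test at a rate near 40%, come close to the formula's 6.3% and 8.3%.

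**4. Interval coverage.** On the log-odds scale each arm contributes variance 1/[n p(1 − p)], multiplied by DE for iLIVE. Unadjusted 95% intervals then cover 93.7% (ICC 0.02) and 91.7% (ICC 0.05) at 40% versus 60%, and 94.3% and 93.2% at the expected 40% versus 10%.

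**5. Power if clustering is counted.** The iLIVE arm has effective size 100/DE, which is 100/1.22 = 82 or 100/1.55 = 65; EUC has 100. A pooled two-proportion test then gives:

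| EUC vs iLIVE | Independent | ICC 0.02 | ICC 0.05 |
|---|---|---|---|
| 10% vs 28% | 91% | 88% | 84% |
| 10% vs 30% | 95% | 93% | 89% |
| 20% vs 38% | 81% | 77% | 71% |
| 40% vs 60% | 81% | 77% | 71% |

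At 10% versus 40%, power is 99.9% for independent men and stays at 92% or more up to m = 20 and ICC 0.10.

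**The case against.** A reader might infer that the 5% error rate is breached and the stated 80% power is lost. The documents do not support either as fact.

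- **Error rate.** Men are randomized individually. If the program changed no man's outcome, sitting in a class would not distort the test and the error would stay nominal. Inflation needs class effects that differ and average to zero. At m = 10 and ICC up to 0.02 the Wald test at a 10% rate does not exceed 5%. This stands, and is why the point is conditional. It does not rescue the intervals, which matter most when the program works.
- **Power.** From the only control rate in the article, 10%, differences of 18 to 20 points keep more than 80% at the values assumed here. The losses at 20% versus 38% and 40% versus 60% rest on rates supplied by this review.
- **Size of the ICC.** The 5% weight loss required for response is targeted largely through individual web sessions, and men may mix across classes; both could lower the ICC. Against that, chair-stand time and gait speed also feed the outcome and are close to what the classes train.
- **Mixed models.** It is tempting to say that they ignore class too. Their random-effects structure is not stated, so that would be read from silence.
- **Left to the analysis plan.** Much detail may sit there, but the article does name the primary model, and that model assumes independence. The general fallback to bootstrapping is prompted by diagnostics such as residual plots, which would not readily show class clustering, and no resampling by class is named.

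**Conclusion.** The point holds in conditional form. Group delivery in one arm, a standard logistic model and a sample size for independent men are all in the article. If the within-class ICC is positive and classes are reasonably stable, the standard error is too small: by a factor of about 1.05 to 1.13 near the null, at 12 per class and ICC 0.02 to 0.05. The conclusion at the expected 40% versus 10% is robust; the exposure is at smaller differences from higher control rates. How large the effect is in this trial cannot be known from the documents. It is a cheap improvement, not a fault that invalidates the design.

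**What to change.** - State how iLIVE men are grouped, and record each man's assigned class and instructor. The Implementation outcomes section shows that class attendance logs are already kept.
- For the primary outcome, prespecify, at least as a sensitivity analysis, cluster-robust standard errors with a small-sample correction, each EUC man being his own cluster. This keeps the marginal odds ratio. The alternative is a class random effect in the iLIVE arm only, which makes the odds ratio conditional.
- Do the same in the models for continuous outcomes.
- Report the class ICC, and state that the power figure assumes no within-class correlation.

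The cost is analysis-plan wording and slightly wider intervals. There would be few clusters (100/12, about eight), so the class variance will be poorly estimated and the small-sample correction matters. If men switch sessions, class should be defined by initial assignment.
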